**Protecol 2008**

**Mental training and childbirth: the effect on pain experience, duration of labour and other birth outcomes**

**Introduction**

**Childbirth and pain**

Labour pain, which represents a great challenge for birthing women, can lead to a negative childbirth experience. Together with loss of control, labour pain accounts for one of the most important factors for a negative childbirth experience [1;2]. A traumatic childbirth experience may result in postpartum depression, posttraumatic stress syndrome, future caesarean section, or a reluctance to have more children [3–5].

Pharmacological methods to relieve labour pain are limited because almost all drugs pass the placental barrier and thereby may have a negative impact on the fetus [6]. Today, epidural analgesia is considered the most effective pain relief method. This technique is, however, associated with side effects such as instrumental deliveries as well as more serious adverse effects for the parturient woman [7]. Furthermore, epidural and other medical analgesia to relieve labour pain may disturb the newborns’ temperature regulation and breastfeeding and crying behaviours [8].

In Denmark, almost 64,000 children are born every year [9]. It is a very important task for society to endeavour to support the parturient woman in an appropriate way to prevent a negative childbirth experience. By focusing on prevention and health promotion, personal and economical costs can be minimised.

**Childbirth, pain, and stress hormones**

Childbirth is an stressful experience, and the concentration of stress hormones is generally higher during childbirth than during pregnancy [10-13]. Pain relief reduces the level of stress hormones, and there is evidence that the levels of both anxiety and pain correlate with the concentration of stress hormones during childbirth [11;14]. Cortisol is a common biomarker for the stress response [15;16].

The measured levels of stress hormones in umbilical cord blood are an indicator of the child’s condition. It has been suggested that stress during pregnancy, childbirth, and the first part of life may affect the programming of the HPA axis in children, with possible consequences for the child's stress sensitivity, behaviour, and attention span later in life [11;17-19].

**Mental techniques for pair relief**

“Mind Body Medicine” is an overall term for various interventions based on the interaction between mind and body. In the industrialised world, there is an increasing interest in these techniques among the adult population. Hypnosis and relaxation are considered internationally to belong to the field of “Mind Body Medicine”[[1]](#footnote-2) [20]. Relaxation can have a beneficial effect in the treatment of depressive conditions and when used by pregnant women to handle the anxiety and stress of giving birth [21;22]. Hypnosis has long been used in connection with various health-related conditions, and it has been shown to have a positive effect in the treatment of several common illnesses [20].

Pain has been one of the indications for this treatment because experience and research show that through use of this technique there is a markedly increased responsiveness of a series of basic physiologic processes and systems, such as pain, the circulation, immunity and muscular and autonomic nerve activity [23]. In studies in which functional magnetic resonance scanning was used, it has been shown that pain hypnosis can change cortical activity in areas of the brain that are important for the generation of the pain [24;25]. Hypnosis has been evaluated as a technique to relieve pain in several experimental studies. Hypnosis has been shown to have a positive effect on both internal pain and external pain, e.g. phantom pain, muscular pain, neurogenic pain and pain due to burns [26;27].

**Studies of childbirth and hypnosis**

Systematic reviews conclude that hypnosis can be advantageous for the birthing woman. Thus the use of pharmacological pain relief and medical interventions can be reduced through this technique [28-30]. A metaanalysis of randomised controlled studies of the use of hypnosis in birthing women found a reduction (relative risk (RR): 0.51; 95% confidence intervals (CI) 0.28–0.95) in the use of pharmacological pain relief. The use of oxytocin augmentation was also reduced (RR: 0.31; 95% CIs: 0.18–0.52).

Studies have shown other effects in pregnant women trained in the use of self-hypnosis. The results indicate that it is possible to achieve a higher pain threshold, more spontaneous births, higher birth weights, improve Apgar scores, prevent preterm delivery and reduce the duration of labour, fear and stress during birth, and postpartum depressions [24;31-35]. Hypnosis may also be applicable to a broad group of women, including target groups that may otherwise be difficult to reach such as vulnerable women [34;36] (table 1, appendix 1).

Generally, there are problems concerning the size of the study groups and the quality of the methods used in many of the studies in this area. For example, the case-control study design is associated with a great risk of false interpretation, most of the randomised studies are small, some studies are not even randomised, and the methods used are not well described. In a metaanalyis of the use of hypnosis during childbirth conducted by Cyna et al. in 2004, only four randomised studies could be included due to methodologic determinants [35-38]. In a systematic literature search in PubMed, the Cochrane Library, and Cinahl, we were able to identify only one randomised controlled study of good methodologic quality [34].

Considering that hypnosis has been reported to have an exceptionally good effect, one can wonder why hypnosis is not more widely used in the healthcare system. This mental training technique has, however, been associated with misunderstandings and negative associations [39]. Unfortunately, as mentioned, the many methodologic problems in many of the studies performed in this area have resulted in a great risk of misinterpretation of the results of these studies. There is therefore need of a well-performed randomised study that includes a sufficient number of birthing women [28-30]. Only by performing such a study can it be finally determined whether self-hypnosis has so many advantages that it should be offered to pregnant women.

For this reason, a large, randomised, controlled study was begin in Australia in 2006 with the primary objective of evaluating the effect of hypnosis on use of medical pain relief [40]. The research team reported a positive effect of a mental training programme developed at their centre and in use for more than 10 years. The intervention involved three 1-hr periods of instruction in self-hypnosis, with a follow-up CD after each visit [24]. Self-hypnosis as a mental training technique has not been evaluated in a Danish obstetric context, and this is important because the organisation and procedures in the Danish healthcare service are different from those in other countries just as is the cultural and mental background of Danish women. If three 1-hr instruction sessions with a follow-up CD can have an effect on labour pain, a big problem could be alleviated with the use of few resources.

It is also of great societal importance to determine whether this mental pain relief technique could influence the choice of future modes of birth and thereby break the rising curve of caesarean deliveries. In addition, it is of great importance to investigate techniques that might reduce the large number of epidural blockages given during childbirth and to study new, effective techniques that can relieve labour pains without side effects. For these reasons, the present project was initiated in dialogue with the Australian research group.

**Aim**

The aim of the study is to investigate the effect of self-hypnosis during childbirth on the following endpoints:

Primary endpoint:

- The use of epidural analgesia during labour

Secondary endpoints:

- Duration of labour
- Birth progression at arrival at birth department
- Birth experience (pain, control, anxiety)
- Medical interventions during birth including mode of delivery
- Saliva cortisol profile at birth and 6 weeks post partum (p.p.)
- Infection during labour and the first 6 weeks p.p. (mother and child)
- Postnatal depression
- Breastfeeding duration
- Child's condition and wellbeing at birth and 6 months later
- Future mode of delivery

**Table 1: Flow and data sources**

| **When** | **What/where** | **Data source** |
| --- | --- | --- |
| Gestational week 10 |  | * Questionnaire from “The Aarhus Birth Cohort” |
| Gestational week 29 | Written information |  |
| Gestational weeks 31–33 | Information meeting |  |
| Gestational weeks 32–34 | Enrolment in the project | * Questionnaire 1 including Wijma Delivery Expectancy/ Experience Questionnaire 1 (*W-DEQ*) |
| Gestational weeks 34–36 | Start of intervention | *Test for hypnotic susceptibility in the intervention group |
| Gestational week 35 |  | *Saliva cortisol sample x 3 |
| Labour | Labour | * Saliva cortisol sample x 3  * Blood sample cortisol umbilical cord (only if economically possible)  *“The Aarhus Birth Cohort  *Medical records |
| 6 weeks p.p.2 |  | * Saliva cortisol sample x 3  * Questionnaire 1 including Wijma Delivery Expectancy/ Experience Questionnaire 1 (*W-DEQ*) and Edinburgh Postnatal depression scale  * Medical records |
| 6 month. p.p. |  | * Questionnaire 3 including Edinburgh Postnatal depression scale |

2. p.p.= post partum (after childbirth)

Saliva cortisol will function as an indicator of the endocrine stress response. In this part of the project, we will only include 260 participants. Thus 100 participants from the intervention group, 100 participants from the active comparison group, and 100 participants from the control group will be included.

**Pilot study:**

Before starting the main study, a pilot study will be performed. The aim of this study is to adjust the intervention and the logistics as well as to identify potential themes not yet integrated into the questionnaires. We will invite about 30 women to participate. Instead of following up with questionnaires at 6 weeks and 6 months post partum, a focus group interview will be performed 3–4 weeks post partum

**Power calculations**

The power calculations are based on the primary endpoint, use of epidural analgesia during childbirth. In 2007, 44% of all primiparas giving birth at Aarhus University Hospital Skejby received epidural analgesia. We presume that the women who want to take part in the project will have a lower frequency in the use of epidural analgesia, 40%, and that the use of epidural analgesia can be reduced to 35% by relaxation techniques, and 25% by self-hypnosis. On the basis of these assumptions, we must include 328 participants in the hypnosis group, 328 participants in the active comparator group, and 152 participants in the control group to obtain a power of 80% (α 0.05 (two-sided)) to detect a difference of 5 percentage points (RR: 0.71) between the intervention and the active comparator groups. By including 152 participants in the control group, we will have a larger power to detect a difference of 15 percentage points (RR: 0.63) in the use of epidural analgesia between the intervention and the control groups.

Because we expect that some participants will develop medical conditions that required epidural analgesia during delivery, give birth prior to receiving their allocated intervention, or give birth by caesarean section, we decide to increase the sample size by 10% in all groups to a total of 890 participants.

Using the estimated number of participants with regard to epidural blockade, a strength of 90% is needed to show a difference of 60 min in duration of labour of between the intervention and control groups. These calculations were performed based on an expected duration of labour of 480 min and 420 min in two groups of the same size, with a range of 220 min in both groups. On this basis, 283 participants will be included in each of these groups.

During the course of the study, an interim analysis will be undertaken after the first 12 months in order to make any necessary adjustments in number of participants

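### The 90% power for a 60-minute difference in labour rests on 283 women per group, but the 2008 control group is 152; the 2010 sizes give about 90–92%, yet the statement was never corrected

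*Protocol*

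**What the plan says.** The Power calculations section of the protocol first sizes the trial on epidural use: 328 women in the self-hypnosis group, 328 in the active comparator group and "152 participants in the control group to obtain a power of 80"% at a two-sided alpha of 0.05. A 10% increase in every group brings the total to 890.

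It then turns to duration of labour, a secondary endpoint. That paragraph opens "Using the estimated number of participants with regard to epidural blockade" and says that "a strength of 90% is needed to show a difference of 60 min in duration of labour" between the intervention and control groups. The stated basis is "an expected duration of labour of 480 min and 420 min in two groups of the same size". The spread is put at 220 min for each group, and the text calls this figure a range. The paragraph ends: "On this basis, 283 participants will be included in each of these groups".

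The 2010 supplement revises the epidural assumptions and prints new group sizes of 446, 446 and 226, with a total of 1097 before a further 10% increase to 1208. It does not mention duration of labour.

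**The concern.** One section gives two sizes for the same control group: 152 (about 167 inflated) and 283. The labour paragraph says that it takes its numbers from the epidural calculation, but it assumes equal groups, and the epidural calculation allocates 328:328:152. The 90% is therefore not a property of the design described beside it.

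The word *range* is a second problem. A reader who took 220 min literally as a range could not get back to 283.

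Duration of labour is in the trial's title, is listed first among the secondary endpoints under Aim, and is the only secondary endpoint with a stated power. Someone interpreting a null result on it would lean on the 90%.

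**Working it through.** **Inputs.** From Power calculations: difference 480 − 420 = 60 min; spread 220 min; power 90%; group sizes 328 and 152; 10% increase. Alpha is not stated for labour duration, so two-sided 0.05 is carried over from the primary endpoint. From the 2010 supplement: 446 and 226, total 1097.

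**Step 1: reproduce 283.** For two equal groups with a common standard deviation,

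n per group = 2 × (1.96 + 1.2816)² × SD² / difference²

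With SD = 220: 2 × 10.508 × 48,400 / 3,600 = 282.5, rounded up to 283. This matches exactly and supports the carried-over alpha; one-sided 0.05 would give 231.

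**Step 2: test the word *range*.** The same formula with other readings of 220 min:
- range = 6 SD (SD 36.7): 8 per group
- range = 4 SD (SD 55): 18 per group
- interquartile range (SD about 163): 156 per group

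Of the readings tried, only a standard deviation of 220 returns 283.

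**Step 3: power with the unequal groups.**

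Power = Φ(60 / [220 × √(1/n₁ + 1/n₂)] − 1.96)

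For 328 v 152 the standard error is 220 × √(1/328 + 1/152) = 21.6 min, so power = Φ(2.78 − 1.96) = 79.4%.

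| Hypnosis v control | Source of sizes | Power |
|---|---|---|
| 283 v 283 | labour paragraph | 90.0% |
| 328 v 152 | 2008, before the 10% increase | 79.4% |
| 361 v 167 | 2008, after the 10% increase | 83.0% |
| 446 v 205 | 2010, controls implied by 1097 | 89.8% |
| 446 v 226 | 2010, controls as printed | 91.6% |

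The inflated sizes are 328 × 1.1 = 360.8 and 152 × 1.1 = 167.2. A t-test calculation changes the 79.4% only to 79.2%.

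**Step 4: the 2010 control number.** 446 + 446 + 226 = 1118, not the stated 1097, and 1097 − 892 = 205. No control size in the document reaches 283; even 226 × 1.1 is only about 249.

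**The case against.** The strongest reply is that the 2008 sizes are superseded. The 2010 supplement replaced them, and on the same assumptions this comparison then has about 90% power. That stands. A reader might infer from the 79% that the trial as finally planned is underpowered for duration of labour; the documents do not support that, because the shortfall belongs to the 2008 sizes only.

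A second reply is that 283 is only a requirement for a hypothetical equal-group comparison. The wording is a statement of how many will be included, and read as a requirement it is still not met by 152 or 167 controls. Nor is 283 the number needed beside a hypnosis group of 328: about 248 controls would give 90% there.

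A third reply is that 83%, not 79%, is the fair 2008 figure. The section adds the 10% for women who, for instance, deliver before their intervention or by caesarean section, so the extra women are a reserve. If all can be analysed, 83% is the ceiling, and it is still below 90%.

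Finally, *range* may be loose English. That is fair: the underlying arithmetic is sound with 220 as a standard deviation, and only the label is wrong. The counts of 8 and 18 per group show which meaning was used; they are not a consequence for the trial.

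**Conclusion.** The point holds as an uncorrected error in the 2008 text. The figure of 283 per group contradicts the control group of 152 in the same section. The 90% does not apply to the 2008 allocation, which gives about 79%, or at most 83%; the chance of missing a true 60-minute difference was about 17–21%, not 10%. The spread is mislabelled.

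The final design is not deficient on this comparison: the 2010 sizes give 89.8% to 91.6%, depending on which control number is right. Nor does the error reach the primary endpoint, whose sample size does not depend on the labour calculation.

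These figures assume two-sided 0.05, a common standard deviation of 220 min, a true difference of 60 min and a normal approximation. Severity is minor.

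**What to change.** In Power calculations:
- Delete the premise "in two groups of the same size" and the closing sentence that puts 283 women in each group.
- Replace *range* with *standard deviation*, and state the alpha used for duration of labour.
- Say that the 2008 sizes gave about 79% power for a 60-minute difference (at most 83% with the inflated groups), not 90%.

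In the 2010 supplement:
- Reconcile the control number first: 226 is printed, while the total of 1097 implies 205.
- Then state the power for duration of labour with the current unequal arms: 89.8% at 446 v 205, or 91.6% at 446 v 226.

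The cost is wording only. No further women are needed.

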**Perspectives**

Preliminary results in the area appear promising and suggest a marked reduction in use of other forms of pain relief, operative procedures during labour, and the negative results of these procedures. If the results of the present studies follow the same tendency as the preliminary results, it can mean economic savings for the entire healthcare system.

**Safety**

In the metaanalysis that studied the effect of hypnosis on pain relief during labour, 19 studies were identified, and in none of them were there any reports of harmful effects of hypnosis. The conclusion is that there is very little basis for a fear of any harmful effects. [29]. This is supported by the Danish Knowledge and Research Centre for Alternative Medicine [41]. In this project, cooperation with highly educated and experienced professionals in the area is given priority. Intervention, the self-hypnosis programme, will be developed in dialog with Australian researchers who have used the technique for more than 10 years in the healthcare system [24]. To achieve the greatest possible safety, only mentally healthy women will be enrolled in the project. Women who attend the first session and then fail to appear will be contacted by telephone to determine the reason for their absence.

**Ethical considerations**

Participants in the project will be offered something more than what is already offered. On the basis of research and experience, the intervention is considered to not have any harmful side effects. Thus no one will be at any disadvantage with regard to the existing prevention and treatment regimens

On the contrary, there is the prospective to study new, effective techniques that can alleviate labour pain without side effects. If the results of the study show a beneficial effect of the studied technique, it can mean that personal and societal expenses will be reduced. The economic perspective is also important to consider in an ethical context, because the release of economic resources will mean that initiatives can be financed in other areas in the Danish healthcare system.

**Permissions**

The research was approved by the Danish Data Protection Agency and the Scientific Ethical Committee for the Region of Central Jutland. The trial will also be reported to ClinicalTrials.gov.

**Supplement to the protocol, 2009**

Before starting the trial, it was decided that the interim analysis would not be undertaken.

**Supplement to the protocol, 2010**

At the start of the study, we performed our power calculations based on the fact that 44% of all primiparas at Aarhus University Hospital Skejby in 2007 had received epidural analgesia. We hypothesised that the observed frequency of epidural analgesia would be 25% in the intervention group, 35% in the placebo effect group, and 40 % in the placebo group.

According to these power calculations, we should include 328 participants in the hypnosis group, 328 participants in the active comparator group, and 152 participants in the control group to obtain a power of 80% (α 0.05 (two-sided)) to detect a difference of 5 percentage points (RR: 0.71) between the intervention and the active comparator groups. By including 152 participants in the control group, we would have a larger power to detect a difference of 15 percentage points (RR: 0.63) in the use of epidural analgesia between the intervention and the control groups.

Because we expected that some participants would develop medical conditions that required epidural analgesia during delivery, give birth prior to receiving their allocated intervention, or give birth by caesarean section, we decided to increase the sample size by 10% in all groups to a total of 890 participants.

In 2010, the study board experienced that in 2009 the general frequency of epidural analgesia in primiparas giving birth at Aarhus University Hospital Skejby had decreased to 34%.Therefore it was decided to adjust the sample size according to this new information.

When the sample size was adjusted, we maintained the same sample ratios between the groups and hypothesised that the observed frequency of epidural analgesia would be 22 % in the intervention group, 30 % in the placebo effect group, and 32 % in the placebo group. To obtain a power of 80% (α 0.05 (two-sided)) in detecting a difference of 8 percentage points (RR: 0.73) between the intervention and the active comparator groups in the use of epidural analgesia and a difference of 10 percentage points (RR: 0.68) between the intervention and the control groups, we should include 446 participants in the hypnosis group, 446 participants in the active comparator group, and 226 participants in the control group, in total 1097 participants. Again, we further increased the sample size with an extra 10% to account for those women that would not be able to comply with their allocated treatment because of obstetric conditions, and reached a sample size of 1208.

**Appendix 1: Studies**  on hypnosis and childbirth

| **Study** | **Sample**  **N** | **Design** | **Intervention** | **Outcomes pain** |
| --- | --- | --- | --- | --- |
| Cyna et al  (2006) (24) | 77/3249  Australia | Case control  Self-selection | 3-4 x Individual sessions in self-hypnosis vs matched controls  Start: After 35 gw | Epidural analgesia |
| Cyna et al  (2004) (29) | 74/68 | Meta-analysis |  | Analgesic medication  RR 0,51 (95%CI; 0,28;0,95) |
| Mehl-Madonna  (2004) (34) | 250/250/(250)  USA | Randomised Controlled Trial  (a machted control group added in analysis) | Hypnosis vs Psychotherapy vs Paired control group  (vs matched control group)  Individual sessions  amount as needed, mean 3 times (Range 1- 60)  Start 1.or 2.trimester | In favor of hypnosis (HG/ PG/ PCG):  Any analgesic medication, (28%/67%/83%)  Epidural analgesia, (28%/67%/83%) |
| Martin et al  (2001) (36) | 22/20 | Randomised Controlled Trial | Hypnosis vs supportive counseling  Both groups 4 x  Hypnosis: Self-hypnosis Hypnoreflexlogymethod incl. information on labour and delivery  Start 20-24 gestational week | -Anaesthesia (45% vs 70%, NS)  -Pitocin (9% vs 30%, NS)  -Postpartum medication (9% vs 55%, NS) |
| Jenkins et al  (1993) (31) | 126/300  136/300 women  Wales | Case control | 6X ½ hour individual hypnosis vs matced controls | Analgesic medication |
| Harmon et al  (1990) (35) | 30/30  USA | Randomised Controlled Trial | Hypnosis vs traditional childbirth education  Training in groups of 15  Both groups 6 x 1 hour on week basis and tapes for homework:  Hypnosis group: Suggestions to ease childbirth  Control group: Progressive relaxation + breathing exercise  Start: End of 2.trimester | In favor of high h (vs low h):  -Use of tranquilizers, p<0.01  -Use of Narcotics, p<0.01 |
| Bran et al  (1987) (32) |  | Clinical study  Self-selection | 2 grupper  4 x hypnose opfulgt af selvhypnose på tape vs psykoprofylakse med åndedrætsøvelser, afspændingsteknik og besøg på fødeafdeling  Start: GW 28 |  |
| Freeman et al  (1986) (38) | Nulliparous women  29/36  United Kingdom | Randomised Controlled Trial | Hypnosis vs traditional childbirth education  Training in groups of 15  Both groups 6 x 1 hour on week basis and tapes for homework:  Hypnosis group: Received individual sessions on week basis from 32 g.a.week focused on relaxation + glove anesthesia  Start: End of 2.trimester | -Analgesic HG vs CG, NS  -High+moderat susceptible vs Poor: less use of epidural analgesia  p<0.01 |
| Guthrie et al  (1984) (42) | 8(8 women | Case control prospective |  | Self-rated pain |
| Rock et al  (1969) (37) | Parturient women  22/18  USA | Randomised Controlled Trial | Hypnosis during childbirth by a hypnotherapist (HG) vs Controls receiving continuous presence of a medical student (CG)  Start: At birth | -Use of analgesic (demetrol and a tranquilizer): HG:52% CG:76%, p<0.05  -Observed comfort: HG more comfortable than CG, p<0.05  -Self-rated pain: HG less pain than CG, p<0.01 |

1. Which also includes biofeedback, cognitive therapy, visualisation and meditation. [↑](#footnote-ref-2)

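### At the printed rates of 22% v 30%, the 2010 figure of 446 per arm gives about 78% power rather than 80%, and power against control cannot be settled until 226 is reconciled with 1097

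*Protocol*

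**What the plan says.** The 2010 supplement re-plans the trial after the hospital's epidural rate in first-time mothers fell to 34%. The assumed rates become "22 % in the intervention group, 30 % in the placebo effect group, and 32 % in the placebo group"; the last two labels are the active comparator and control arms.

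One sentence then claims 80% power at two-sided 0.05 for two comparisons. The first is hypnosis against active comparator: "To obtain a power of 80% (α 0.05 (two-sided)) in detecting a difference of 8 percentage points (RR: 0.73) between the intervention". The second is "a difference of 10 percentage points (RR: 0.68) between the intervention and the control groups". The sizes said to achieve this are "446 participants in the hypnosis group, 446 participants in the active comparator group, and 226 participants in the control group, in total 1097 participants". The supplement also says "we maintained the same sample ratios between the groups", and the earlier sizes it repeats are "328 participants in the hypnosis group, 328 participants in the active comparator group, and 152 participants in the control group".

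After this, 10% is added for women who cannot comply with their allocation for obstetric reasons, giving a final 1208. The 80% is therefore attached to the sizes before the 10% is added.

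**The concern.** The supplement prints everything needed to check its claim: rates, significance level, power and arm sizes. For hypnosis against active comparator they do not agree, because 446 per arm is too few for 80% at 22% v 30%.

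For hypnosis against control the check cannot be completed, because the control arm has two sizes: the printed 226, and the smaller number left by the printed total and the kept ratio.

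At stake is the justification for the revised sample size on the primary endpoint. A reader who takes 80% as the power of the design before the allowance for non-compliance is given a figure that the printed inputs do not support.

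**Working it through.** **Inputs.** All are from the 2010 supplement: rates 22%, 30% and 32%; two-sided 0.05 (z = 1.96); 80% power (z = 0.8416); arms 446/446/226; total 1097; ratio 328:328:152; 10% increase; final 1208.

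**Formula.** Two-proportion normal approximation with pooled variance under the null and no continuity correction, for equal arms:

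n = [1.96·√(2p̄(1−p̄)) + 0.8416·√(p1(1−p1) + p2(1−p2))]² / (p1−p2)²

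**1. Reproduce the 2008 figure.** The stated 328 per arm belongs to 25% v 35%. The text calls this a 5-point difference, but its RR of 0.71 is 25/35. With p̄ = 0.30: 1.96·√0.42 = 1.2702 and 0.8416·√0.415 = 0.5422. The sum is 1.8124, its square 3.2847, and dividing by 0.01 gives 328.5. This matches the plan to within one woman, so the formula is a fair one to hold the 2010 figure to.

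**2. Same formula for 22% v 30%.** With p̄ = 0.26: 1.96·√0.3848 = 1.2158 and 0.8416·√0.3816 = 0.5199. The sum is 1.7357, its square 3.0127, and dividing by 0.0064 gives 470.7, so **471 per arm**. The stated 446 is 25 fewer.

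**3. Power at 446 per arm.** Null standard error √(0.26·0.74·2/446) = 0.02937; alternative √(0.3816/446) = 0.02925. Then (0.08 − 1.96·0.02937)/0.02925 = 0.767, which gives **77.8%**.

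**4. Other standard methods for 22% v 30%.**

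| Method | n per arm for 80% | Power at 446 |
|---|---|---|
| Pooled | 471 | 77.8% |
| Unpooled | 468 | 78.1% |
| Arcsine | about 469 | 78.0% |
| Continuity-corrected | 496 | 75.5% |

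A one-sided test would need 371 (396 with correction). None of these gives 446.

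**5. Size of the control arm.**
- Printed arms: 446 + 446 + 226 = 1118, not 1097.
- From the printed total: 1097 − 892 = 205.
- From the kept ratio: 446 × 152/328 = 206.7, so 207.
- With the 10% added: 1097 × 1.10 = 1206.7, close to 1208; 1118 × 1.10 = 1229.8, which is not.
- By arm: 446 × 1.10 = 490.6 (491) and 205 × 1.10 = 225.5 (226); 491 + 491 + 226 = 1208.

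The last line suggests that 226 is the inflated control number placed in the list before inflation. The supplement does not say so.

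**6. Power for 22% v 32% with 446 in the hypnosis arm.** For 226 controls the pooled rate is 0.2536 and the standard errors are 0.03553 (null) and 0.03671 (alternative). Then (0.10 − 1.96·0.03553)/0.03671 = 0.827, which gives 79.6%. The same steps for the other sizes give:

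| Controls | Basis | Power, pooled | Power, unpooled |
|---|---|---|---|
| 226 | printed | 79.6% | 77.8% |
| 207 | kept ratio | 77.4% | 75.1% |
| 205 | total of 1097 | 77.1% | 74.8% |

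For 80% with 446 in the hypnosis arm, 230 controls are needed. At the ratio 328:152, 478 and about 222 are needed.

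**7. The inflated sample.** At 491/491/226, power is 81.6% for 22% v 30% and 80.9% for 22% v 32%, if every woman is analysed and the assumed rates hold.

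**The case against.** **Rounding of the rates.** The rates are printed as whole percentages. With 21.8% v 30.0%, which would print the same way, the formula gives 446.9 per arm, and 446 gives 79.9%. There is a faint hint of this in the text: the printed RR of 0.68 for the control comparison is not 22/32 = 0.6875 (0.69), whereas 21.8/32 = 0.681. So unrounded inputs are possible. But the protocol states 22%, and an RR of 0.68 could equally be a slip. What stands is that the gap is small, equivalent to a detectable difference of about 8.2 points instead of 8, and that giving the unrounded rates, if they were used, would be a complete answer for this comparison.

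**The 10% increase covers it.** The sample of 1208 does exceed 80% for both comparisons under the conditions in step 7, and the reader should be told so. But the supplement assigns the 10% to women who cannot comply, and it claims 80% before adding them. The increase does not make the claim for 446 correct.

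**The printed control arm passes.** With 226, pooled power is 79.6%, which is 80% after rounding. This stands. A reader might infer that the control comparison simply has 77%. The documents do not support that without condition, because 226 is the number actually printed.

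**Size.** The shortfall in power is 2.2 points pooled and 1.9 unpooled, on guessed event rates. That limits the weight of the point. The required number is still off by 22 to 25 per arm (unpooled and pooled), whereas the 2008 figure reproduces to within one.

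**Conclusion.** Wrong as written, and minor. At the printed 22% v 30%, 446 per arm gives about 78% power; 80% needs 471 (468 unpooled, 496 with continuity correction). This rests only on figures in the 2010 supplement and on a formula checked against the 2008 figure, and it does not involve the control arm.

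For 22% v 32% the conclusion is conditional: 79.6% if the control arm before inflation is 226, about 77% if it is 205 to 207. The total, the ratio and the final 1208 favour the smaller number, but the supplement leaves it open.

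Two stronger readings are not supported:
- A reader might infer that the trial is underpowered. It is not shown to be: the planned 1208 passes 80% for both comparisons if all women are analysed at the assumed rates.
- A reader might infer that 446 was taken from the calculation in the Power calculations section for "a difference of 60 min in duration of labour", since those inputs re-run at 328:152 give about 446 and 207. But that calculation uses equal groups and arrives at 283 each, the 2010 supplement does not mention duration of labour, and 446 + 446 + 207 = 1099, not 1097. It is conjecture.

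**What to change.** Keep recruitment as it is and amend the 2010 supplement:

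1. For hypnosis against active comparator, restate the power as about 78% with 446 per arm at 22% v 30%. Alternatively, give 471 per arm as the number for 80%, or state the unrounded rates if those produced 446.
2. Reconcile the control arm of 226 with the total of 1097 and the final 1208, and label each number as before or after the 10% increase.
3. State the power for 22% v 32% for the control arm that results: 79.6% with 226, about 77% with 205 to 207.
4. Add that the inflated sample (about 491/491/226 = 1208) gives about 82% and 81%, only if all women are analysed and the assumed rates hold.

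The cost is wording only. The stated power becomes slightly less favourable; recruitment, endpoint and analysis are unchanged.
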